We will initiate a stepped wedge randomized controlled trial involving 1) 35 clinics receiving a performance coaching intervention and 2) a treatment as usual (TAU) condition for all clinics not participating in the intervention. Additionally, qualitative interviews with stakeholders and surveys of all 550 outpatient clinics will be conducted at three different points in time (years 1, 3, and 4). We will use administrative data from 2021–2027, including records from the Office of Addiction Services and Supports (OASAS) treatment registry, Medicaid, and vital statistics, to monitor client outcomes. This concurrent mixed-methods study [94] will evaluate the impact of the OASAS QM2 strategy on patient outcomes and statewide stakeholders, focusing on retention in care and adverse events (emergency department visits, hospitalizations, and mortality). Clinics will be randomized to one of five sequences, varying the timing of the intervention between years 2 and 4.

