## Materials and methods

### Project 3 aims: Conduct a stepped-wedge trial that includes two conditions: 1) 35 clinics receiving a performance coaching intervention and 2) a treatment as usual (TAU) condition for all clinics not participating in the intervention to examine the effect of the OTP intervention on THD, retention in care, and adverse events

The SPIRIT checklist was used as a guide for reporting this study protocol (Fig 1). To assess the impact of the OASAS QM2 strategy on care retention and adverse events using a stepped-wedge, mixed-methods design across SUD treatment clinics. Clinics will be recruited to participate in this stepped wedge trial by State partners via email invitations, announcements via State listservs, and announcements at relevant meetings to contact the Project Manager or the Principal Investigators. A total of 35 clinics will be recruited after October 2025. The aim of the intervention is to help clinical staff interpret their quality measures and implement subsequent quality improvement efforts through facilitators. The intervention will be six months long for each clinic and be informed by the i-PARIHS model [95].

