Before the trial begins, clinics receiving the QM2 intervention will be randomized into six cohorts of six-month long interventions over three years. Clinics are randomized to onset of intervention in one of six time periods over the three years of the intervention rollout (years 2–4 of the project) and tracked using administrative data. Administrative data will be used for all clinic clients during each of the seven six-month periods (n ≈ 350/clinic) will be drawn from administrative data. The first six-month period will be a baseline prior to any intervention. Six clinics will be assigned randomly to one of six time periods for onset of intervention. Using administrative data, we will track clients within each clinic over four years, including a pre-intervention six-month baseline period. During the same four-year period, clients in clinics not participating in the stepped-wedge trial will be tracked to better understand changes in outcomes under treatment as usual (TAU) and to compare the outcomes of those clinics with clinics receiving the quality management intervention. We anticipate a final study population of approximately 91,000 individuals per year who are receiving treatment from one of the 571 enrolled outpatient substance use treatment programs. Because this is a stepped-wedge trial, all clinics (and as a result all clients within the clinics) will eventually get the intervention, the randomization will have to do with when the clinic is randomized rather than being assigned to a control or intervention group. Fig 2 illustrates the structure of the stepped-wedge trial.

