*Statistical Analyses of the Proposed Stepped-Wedge Trial:* Analyses will begin with examination variable distributions, appropriate transformations, and patterns for, followed by formal imputation methods if needed [110–112]. We will use Generalized Linear Mixed Models (GLMM) for the stepped-wedge design [106].

*Power Analysis for Primary Outcome Statistical power:* Power estimation for specific outcomes was conducted using PASS 2022 software and Monte Carlo simulation [113]. Sample size and baseline rates (μ) were estimated using administrative data. For 80% power, α = 0.05, ICC = 0.05, and a 5-crossover-point stepped-wedge-RCT with 7 clinics starting at each point, power calculations indicate 80% power to detect a small decrease (RR = 0.93) in adverse events with 35 clinics and 350 clients per clinic per 6-month period (n ≈ 73,500 total observations). This corresponds to a decrease from 0.23 to 0.21 events per 6 months. In racial/ethnic subgroups (10% of clients, n ≈ 35 per site), power remains 80% to detect a modest decrease (OR=0.78), from 0.23 to 0.18.

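### The article describes two incompatible stepped wedges: six cohorts of six clinics over seven periods in the randomisation text, five sequences of seven over six periods in the power text

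*Protocol article*

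**What the plan says.** **Randomisation text** (Materials and methods, Project 3 aims, the paragraph after the description of the coaches):
- "clinics receiving the QM2 intervention will be randomized into six cohorts of six-month long interventions over three years"
- "Six clinics will be assigned randomly to one of six time periods for onset of intervention"
- "Administrative data will be used for all clinic clients during each of the seven six-month periods", at about 350 clients per clinic
- "The first six-month period will be a baseline prior to any intervention"

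**Introduction** (last paragraph): "Clinics will be randomized to one of five sequences, varying the timing of the intervention between years 2 and 4".

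**Power analysis** (Data and analytic plans, Project 3): "a 5-crossover-point stepped-wedge-RCT with 7 clinics starting at each point", with 35 clinics, 350 clients per clinic per six-month period, about 73,500 observations, ICC 0.05, α 0.05, and 80% power for a rate ratio of 0.93 from a baseline of 0.23.

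**Number of clinics:** the Project 3 aims section states "A total of 35 clinics will be recruited after October 2025". The Abstract, the Introduction and the power analysis also give 35.

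**Interviews:** 72 staff interviews are planned, with at least one clinical and one executive interviewee at each clinic.

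**The concern.** Each set of statements is coherent alone, but the two disagree on the number of sequences, the clinics per sequence, the total number of clinics and the number of periods. This is more than a slip in one figure.

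The article says clinics are randomised before the trial begins. The allocation list needs the number of sequences and the number of clinics in each, and the text gives two answers. The primary mixed model has a fixed effect for each period and an intervention indicator that switches on at each clinic's onset, so its layout depends on the same choice. The only power statement is for the five-sequence wedge, while the most detailed account of the randomisation is the six-cohort wedge.

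**Working it through.** **1. Number of clinics**
- Randomisation text, read as six clinics per onset period: 6 × 6 = 36.
- Power text: 5 × 7 = 35.
- 35 is not divisible by six. The nearest split is 6, 6, 6, 6, 6, 5.

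**2. Number of periods**
- Randomisation text: one baseline + six onsets = 7, as stated.
- Power text: not given in words, but fixed by the total. Observations = clinics × clients per clinic-period × periods, and 35 × 350 × 6 = 73,500, exactly the stated figure. Six periods are one baseline plus five steps, which agrees with five crossover points.
- With seven periods: 35 × 350 × 7 = 85,750 (12,250 more), or 36 × 350 × 7 = 88,200 (14,700, or 20%, more).

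**3. Interviews**
- 2 × 36 = 72 and 2 × 35 = 70. Because the text says at least one clinical interviewee per clinic, 70 is a minimum at 35 clinics and 72 is allowed.

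**4. Effect on power**

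The Hussey–Hughes variance for a model with fixed period effects and a random clinic intercept is

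Var(δ) = Iσ²(σ² + Tτ²) / {(IU − W)σ² + (U² + ITU − TW − IV)τ²}

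Here I is clinics, T is periods, σ² is the within-clinic variance of a clinic-period mean and τ² is the between-clinic variance. U is the number of treated clinic-periods, W the sum over periods of (treated clinics)², and V the sum over clinics of (treated periods)².

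From the article: 350 per clinic-period, ICC 0.05, rates 0.23 and 0.23 × 0.93 = 0.2139, so δ = 0.0161. Assumed: two-sided α 0.05 and the form of the variance.

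Worked case, binomial variance averaged over the two rates:
- (0.23 × 0.77 + 0.2139 × 0.7861)/2 = 0.1726
- σ² = 0.1726/350 = 0.000493
- τ² = 0.1726 × 0.05/0.95 = 0.00909
- Power = Φ(δ/SE − 1.96)

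| Layout | U | W | V | SE | δ/SE | Power |
|---|---|---|---|---|---|---|
| 5 × 7, 6 periods | 105 | 2,695 | 385 | 0.00548 | 2.94 | 83.6% |
| 35 clinics as 6,6,6,6,6,5, 7 periods | 125 | 3,205 | 545 | 0.00504 | 3.20 | 89.2% |
| 6 × 6, 7 periods | 126 | 3,276 | 546 | 0.00495 | 3.25 | 90.2% |

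For example, in the first row U = 7 × (1+2+3+4+5) = 105, W = 49 × (1+4+9+16+25) = 2,695 and V = 7 × 55 = 385.

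Reproducing the stated effect size: with binomial variance at 0.23, the 5 × 7 layout over six periods detects a rate ratio of 0.932 at 80% power, which rounds to the stated 0.93.

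The article does not fix the variance form. Reasonable conventions (variance at either rate or their mean; ICC set against the within-clinic or the total variance) give:

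| Layout | Binomial | Poisson |
|---|---|---|
| 5 × 7, 6 periods | about 83–86% | about 72–76% |
| 35 clinics in six cohorts, 7 periods | about 88–91% | about 79–83% |
| 6 × 6, 7 periods | about 89–92% | about 80–84% |

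Under every convention the seven-period layouts have more power than the powered one. The absolute level also depends on how strongly a clinic's rate correlates across periods, which is not given. At a cluster autocorrelation of 0.95 and binomial variance, power is about 57% for 5 × 7 and 65% for 6 × 6; the order is unchanged.

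**The case against.** **The powered design may be the one intended.** The Introduction says five sequences, agreeing with the power analysis, and 35 clinics is stated in many places. A drawable five-by-seven list exists. This stands. A reader might infer that the trial will run a design other than the one powered, but the text does not support that; it leaves open which wedge will be run.

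**Power does not suffer.** This also stands. A reader might infer that the mismatch leaves the trial underpowered, but the six-cohort layout has more power than the powered one in every variant checked.

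**The 72 interviews are not an error.** Also correct. The figure fits 36 clinics neatly, but the minimum wording allows it with 35, so it is weak corroboration only and needs no correction.

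**Fig 2 or a fuller protocol may resolve it.** Fig 2 is not available here. It could show which wedge is meant, but it cannot make both statements true. Nor is this a matter of an article leaving detail out, since the number of sequences is stated outright with two different values.

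**Duration is unsettled for other reasons.** The randomisation paragraph gives both seven six-month periods (3.5 years) and four years of tracking, and the status section has data collection ending in December 2026. So choosing a wedge will not by itself fix the length of follow-up.

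**Conclusion.** The contradiction holds. The randomisation text describes 36 clinics in six cohorts over seven periods, with 88,200 observations (85,750 if 35 clinics are used). The Introduction and the power analysis describe five sequences, with seven clinics each and 73,500 observations, hence six periods. The number of sequences, clinics per sequence, periods and observations is therefore undefined, and 35 clinics cannot be allocated as the randomisation paragraph states.

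The arithmetic on clinics and periods rests only on figures in the article, reading six clinics as the number per onset period. Even without that reading, six cohorts against five sequences and seven periods against six remain in conflict. The power comparison rests on a random clinic intercept only, two-sided α and an assumed variance form. It shows a difference of roughly 6 to 8 percentage points in favour of six by six over seven periods, so the harm is an ambiguous allocation and an untied power statement. The point should be settled before randomisation.

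**What to change.** Before the allocation list is drawn, the investigators should choose one wedge and state it identically in the Introduction, the randomisation paragraph, the power analysis and Fig 2.

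- **If five sequences of seven clinics are kept** (one baseline plus five steps, six periods), which fits the 35 clinics and the power section: correct the randomisation paragraph to this and leave 73,500 as it is.
- **If six cohorts are kept with 35 clinics:** state the unequal split 6, 6, 6, 6, 6, 5 over seven periods, restate total observations as 85,750, and rerun the power calculation for that layout, giving the variance form and sidedness used.

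In either case, reconcile the follow-up length, since the randomisation paragraph gives both seven six-month periods and four years. The interview target of 72 can stay.

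The cost is wording, the allocation list and at most one power rerun.

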**Fig 2 pone.0330882.g002:**
[figure not shown]
Stepped-Wedge Trial Diagram.

The intervention will be delivered to clinic leadership and staff. Zoom meetings with program directors will confirm enrollment and outline the timeline and expectations. We will use maximum variation purposeful sampling by recruiting clients from participating clinics in urban and rural locations as well as areas with variation in population characteristics. Clinic recruitment will be stratified by region (downstate, central, and western New York). Eligible clinics are OASAS-licensed specialty SUD outpatient programs serving at least 50 OUD clients annually. Further, we will recruit clients who are on a variety of MOUD schedules and ensure that we have representation based on gender, race, and ethnicity.

We will examine clinic staff and leadership’s perceptions of the intervention using surveys and semi-structured interviews [97–99]. The Klein implementation survey [100,101] will be administered to clinic staff at 6-months post-intervention. Semi-structured interviews (n = 72) will be conducted with at least one clinical and one member of clinic executive leadership at each clinic at the end of the six-month intervention phase. An interview guide will be created to reflect the dimensions of the i-PARIHS model [102–105]. In order to inform replication and dissemination of this intervention model, the Coaches will complete logs after each interaction with a study site [97]. Master’s-level interviewers with qualitative experience, supervised by Drs. [name] and [name], will conduct all ~ 60-minute interviews. Field notes will be recorded post-interview.

### Component 1: Conduct qualitative interviews with stakeholders at years 1, 3 and 4 to examine clinic staff and leadership attitudes, experiences, and behaviors related to implementing the clinic intervention

We will recruit at least 50 participants per year in years 1, 3, and 4 of the project for 1:1 semi structured qualitative interviews until saturation is reached. Semi-structured interviews (n = 72) will be conducted with stakeholders. This includes at least one clinical and one member of outpatient executive leadership at each clinic at the end of the six-month intervention phase. An interview guide will be created to reflect the dimensions of the Health Equity Implementation Framework (HEIF), including patient-provider encounter factors from the Kilbourne framework as well as implementation factors from the i-PARIHS model. Client interviews (n = 40) from participating clinics will explore experiences related to quality of care in SUD treatment program, notably among Black/African American and Latinx clients.

### Component 2: Conduct surveys of clinics in years 1, 3, and 5 of the project to examine changes over time in the effects of the QM2 study on programs

OASAS will conduct surveys of all 550 outpatient clinics in years 1, 3, and 5 of the project. The surveys will explore change over time in provider practices (e.g., harm reduction strategies, evidence-based practices, quality improvement activities) and environmental influences related to the OASAS QM2 study (e.g., related experiences with patients/families and insurers, development of performance-based contracts). OASAS regularly surveys all clinics within its system to assess system needs. Historically, the response rate for these survey was about 60%. Surveys will be administered through the OASAS online survey data collection portal. The surveys will address the extent to which the new measures are used in quality improvement, and the burden of collecting using qualitative measures.

### Data and analytic plans

#### Project 3: Stepped-wedge trial.

*Quantitative Methods:* We will utilize Generalized Linear Mixed Models (GLMMs), which are commonly applied in the analysis of stepped-wedge trial [106,107]. The models will be structured as follows:

$$F(\mu_{ijk})=\mu +\beta_{j}+{\delta X}_{ij}+\alpha_{i}+\phi_{ik},\;\alpha_{i}\sim N\left(\text{0},\tau_{\alpha }^{\text{2}}\right),\;\gamma_{ij}\sim N(\text{0},\tau_{\phi }^{\text{2}})$$

where $\beta_{j}$ represents a fixed effect for time, $X_{ij}$ is an indicator for intervention in clinic *i* at time *j* (coded 0 for the control condition, then 1 from the start of the intervention in the clinic until the end of the study), and δ denotes the intervention effect. The models include random effects to account for clustering at both the clinic and individual patient levels, which are assumed to follow a normal distribution with mean zero and variances $\tau_{\alpha }^{\text{2}}$ and $\tau_{\phi }^{\text{2}}$, respectively. We will estimate the intervention effect while controlling for secular trends and adjusting for clustering within clinics ($\alpha_{i}$) and individual ($\phi_{ik}$), using mixed effects modeling with a binary distribution and logit link function. The models will be fitted using the *glmmTMB* package in R software [108,109]. The primary outcome will be adverse events, and the fixed-effects coefficients for the intervention effect, exponentiated, will indicate the extent to which the intervention changes the rate of adverse events. An offset term can be included to capture client differences in time at risk due to timing of treatment entry.

TAU clinics will be included in the model with an indicator variable. A post-hoc test of the intervention effect coefficient will compare TAU and performance coaching, and a TAU-by-time interaction will assess time trends within the TAU group. The GLMM analysis will be expanded by adding the clinics not receiving the performance coaching intervention during the study period. For TAU clinics, the intervention indicator will be coded 0 in all periods. This provides an additional estimate of trends ($\beta_{j}$) in outcomes in a much larger sample of clinics. Because the fixed effect for time ($\beta_{j}$) is estimated, the intervention effect (δ) can be interpreted as the degree to which performance coaching results in a lower rate of adverse events than what would be expected due to time alone in the absence of intervention.

If we observe significant treatment effects (e.g., reduced adverse events) from the performance coaching intervention, we will conduct follow-up analyses to strengthen causal inference. Drawing on methods from treatment mechanism research, we will test whether hypothesized mediators (e.g., person-centered care, retention in treatment) are associated with outcomes. We will also examine moderation by population characteristics and regional variation (e.g., gender, location), as well as provider-level differences in implementation. Lagged treatment effects will be assessed using interaction terms between treatment and time since intervention start by cohort. These exploratory analyses will inform interpretation and guide qualitative inquiry.

*Data and specification:*

We will join multiple administrative data sources from New York State for years 2021–2027 to form our analytical dataset. We will use Client Data System (CDS), Medicaid claims, and NYS vital statistics data to form the analytic dataset. The OASAS treatment registry (CDS) will provide extensive clinical data on clients at treatment admission and will include descriptions of providers through the provider data system (PDS). Medicaid will provide medical diagnoses, healthcare services, SUD treatment services, and medication utilization data. The New York State Vital Statistics will be received from the outpatient clinics in the form of all-cause mortality for clients participating in the trial. Additional OASAS data will provide operational and staffing information for each clinic. To date, 75% of clients in the OASAS registry have been linked to Medicaid claims data.

Quality measures from Project 1 will encompass patient, clinic, and organizational factors, including demographics, clinical complexity, substance use patterns, prior healthcare utilization, community access, substance use trends, resources, psychosocial interventions, clinic structure, staffing, and MOUD use and retention. Primary outcomes include adverse events, healthcare utilization, and mortality. Adverse events are defined as SUD-related hospitalizations or emergency department visits, including overdose, within 12 months of treatment entry. Healthcare utilization includes all-cause emergency department visits or hospitalizations within the same timeframe. Mortality will be assessed as all-cause mortality. Outcome variables will be risk-adjusted to account for client health status.

*Statistical Analyses of the Proposed Stepped-Wedge Trial:* Analyses will begin with examination variable distributions, appropriate transformations, and patterns for, followed by formal imputation methods if needed [110–112]. We will use Generalized Linear Mixed Models (GLMM) for the stepped-wedge design [106].

*Power Analysis for Primary Outcome Statistical power:* Power estimation for specific outcomes was conducted using PASS 2022 software and Monte Carlo simulation [113]. Sample size and baseline rates (μ) were estimated using administrative data. For 80% power, α = 0.05, ICC = 0.05, and a 5-crossover-point stepped-wedge-RCT with 7 clinics starting at each point, power calculations indicate 80% power to detect a small decrease (RR = 0.93) in adverse events with 35 clinics and 350 clients per clinic per 6-month period (n ≈ 73,500 total observations). This corresponds to a decrease from 0.23 to 0.21 events per 6 months. In racial/ethnic subgroups (10% of clients, n ≈ 35 per site), power remains 80% to detect a modest decrease (OR=0.78), from 0.23 to 0.18.

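### The primary GLMM has no clinic-by-period random effect, so if clinic rates drift beyond the common time trend it will understate the standard error of the coaching effect

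*Protocol article*

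**What the plan says.** Under Data and analytic plans, Project 3: Stepped-wedge trial, the protocol article sets out the primary model. On the link scale it is μ + β_j + δX_ij + α_i + φ_ik: a fixed period effect, the intervention indicator, a clinic intercept and a client effect. The prose confirms this: "The models include random effects to account for clustering at both the clinic and individual patient levels". The fit is to be made "using mixed effects modeling with a binary distribution and logit link function".

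The distribution list beside the equation does not match the predictor. It gives α_i a normal distribution. It then gives one to γ_ij, a symbol indexed by clinic and period, with the variance symbol that belongs to φ. γ_ij is not in the predictor and is not defined. φ_ik is in the predictor but has no distribution in the list.

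The power paragraph in the same section reads: "For 80% power, α = 0.05, ICC = 0.05, and a 5-crossover-point stepped-wedge-RCT with 7 clinics starting at each point". It claims "80% power to detect a small decrease (RR = 0.93) in adverse events", and describes this as a fall from 0.23 to 0.21. The sample behind the claim is 350 clients in each of 35 clinics per half-year, about 73,500 observations in all. The paragraph gives one ICC and no correlation between periods.

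**The concern.** As written, the model assumes that two clients of the same clinic are equally correlated whether they are treated in the same half-year or several years apart. The period effect β_j removes trends common to all clinics. It does not remove changes specific to one clinic, for example in staffing, local drug supply or unmeasured case-mix. A Gaussian model could absorb part of such variation in its residual, but a binary logit model has no free residual variance. The client effect does not help, because it does not capture a shift shared by all clients of a clinic in one period.

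With 350 clients per cell, sampling error is small and modest clinic-specific drift is of comparable size. If drift exists and the model ignores it, the confidence interval for the coaching effect is too narrow, and the primary test can declare a benefit too often. A power figure obtained without that variance would also be too optimistic.

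**Working it through.** **Inputs.** From the protocol article: 5 crossover points with 7 clinics each, m = 350 per clinic-period, ICC = 0.05, α = 0.05, baseline rate 0.23, RR = 0.93. The total 35 × 350 × 6 = 73,500 agrees with the stated number of observations and implies 6 periods. Assumed: a two-sided test, and the CAC, meaning the between-period correlation within a clinic divided by the within-period correlation.

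**Variance components on the rate scale.** v = 0.23 × 0.77 = 0.1771.
- Clinic: ICC × CAC × v
- Clinic-by-period: ICC × (1 − CAC) × v
- Sampling error of a cell: (1 − ICC) × v / m

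**Scale of the problem.** The sampling SD of a cell rate is √(0.95 × 0.1771 / 350) = 0.0219. At CAC 0.95 the clinic-by-period SD is √(0.05 × 0.05 × 0.1771) = 0.0210, almost the same. The target difference is 0.23 × 0.07 = 0.0161.

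**Formulas.** Generalised least squares on clinic-period means with fixed period effects. Let D be the design matrix of a clinic, V its true covariance, and W the inverse of the covariance without the clinic-by-period term.
- Model variance: A⁻¹, with A = Σ D′WD
- Actual variance: A⁻¹ (Σ D′WVWD) A⁻¹
- Type I error: 2Φ(−1.96 × SE_model / SE_actual)
- Power with the term included: Φ(0.0161 / SE − 1.96), where SE² is the intervention element of (Σ D′V⁻¹D)⁻¹

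**The plan's own figure.** At CAC 1 the SE is 0.00541. The detectable difference at 80% power is 2.80 × 0.00541 = 0.0152, so RR = 1 − 0.0152/0.23 = 0.934, which rounds to the stated 0.93. Power at exactly 0.93 is 85% at CAC 1 and 78% at CAC 0.99.

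**Results, ICC 0.05.**

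| CAC | Model SE | Actual SE | Type I error | Power at RR 0.93, term included | Detectable RR at 80% |
|---|---|---|---|---|---|
| 1 | 0.0054 | 0.0054 | 5.0% | 85% | 0.934 |
| 0.99 | 0.0054 | 0.0059 | 7.2% | 78% | 0.928 |
| 0.95 | 0.0054 | 0.0075 | 15.7% | 58% | 0.909 |
| 0.90 | 0.0054 | 0.0091 | 24.4% | 43% | 0.890 |
| 0.80 | 0.0054 | 0.0117 | 36.4% | 29% | 0.860 |

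Using the variance at the midpoint of the two rates instead of at baseline raises the power figures by about one point and leaves the type I error unchanged.

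**Check by simulation.** A binomial logit GLMM with a clinic intercept and period effects was fitted to simulated null trials.
- 250 trials per setting: rejection 5.6% (CAC 1), 13.2% (0.95) and 25.6% (0.90).
- 300 trials per setting: rejection 3.7% (CAC 1), 13.3% (0.95), 26.3% (0.90) and 40.0% (0.80). At CAC 0.90 the empirical SD of the log odds ratio was 0.055 against a mean model SE of 0.031.

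**Sensitivity: type I error at CAC 0.95, 0.90 and 0.80.**
- ICC 0.02: 9%, 13%, 21%
- ICC 0.01: 7%, 9%, 13%
- ICC 0.05 with a within-client correlation of 0.3 (assumed) that the working model includes: 20%, 30%, 43%
- ICC 0.05 with 515 TAU clinics added (550 − 35, assumed 160 clients per period): 15%, 24%, 36%
- ICC 0.05 with six cohorts of six clinics over seven periods, as in the Project 3 aims section: 16%, 24%, 36%

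**The case against.** A reader might infer that the type I error of this trial is well above 5%. The article does not support that as a fact. It gives no CAC, and at 0.99 the error is only about 7%. Every inflated figure depends on clinic-specific drift of the assumed size.

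A reader might also infer that the power calculation demonstrably omits the term and reproduces only at CAC 1. That is too strong. Power at exactly 0.93 is nearer 85% than 80% at CAC 1, and the nearest match is about 0.99. If the target is taken literally as 0.23 to 0.21, a CAC of about 0.956 gives about 80%. The simulation inputs are not shown. The single ICC and the match near 1 make omission the likelier reading, but it remains an inference.

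Risk adjustment is planned for client health status, and the abstract adds individual and community characteristics. This would absorb some measured case-mix drift and could lower the residual ICC, which is why ICC 0.01 and 0.02 are shown. The inflation shrinks but does not vanish.

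The simulated model left out the client effect, the TAU clinics and the risk adjustment, so it is not a refit of the full planned model. The analytic variants indicate that the first two do not remove the inflation. TAU clinics would, however, raise power: with the term included and the assumed 515 clinics, power at RR 0.93 is about 92%, 79% and 58% at CAC 0.95, 0.90 and 0.80. The article's power statement rests on the 35 clinics alone.

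Finally, γ_ij may be the remnant of an intended clinic-by-period term. The predictor and the prose both exclude it, so the model as published lacks the term, and the equation needs correction on either reading.

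**Conclusion.** The concern holds conditionally. The article commits to a specific predictor, link and software package, so this is a stated choice of model rather than a detail left to the analysis plan. The 5% level is close to correct only if clinic rates are almost perfectly stable around the common trend, with CAC about 0.99 or more at the protocol's ICC of 0.05. The article neither states nor supports that assumption. For CAC 0.95 to 0.80, type I error is about 13–40% at ICC 0.05 and 7–13% at ICC 0.01. With the term included and 35 clinics, power at RR 0.93 is about 58% to 29% over the same CAC range at ICC 0.05. These sizes rest on the assumed CAC, equal cell sizes, a two-sided test and no risk adjustment. The mismatch between the predictor and its distribution list is certain.

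**What to change.** Add a clinic-by-period random intercept to the primary model: in glmmTMB, `(1|clinic) + (1|clinic:period)`, with `(1|client)` where clients contribute several rows. Correct the equation so that each random effect in the predictor has its own distribution and its own variance. Estimate the ICC and CAC from the administrative data from 2021 onward, which the study already plans to use, and restate power or the detectable RR over a range of CAC around that estimate.

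The cost is one model term, a corrected equation and a rerun of the power calculation. Confidence intervals will be wider and the stated power less favourable. If the estimated CAC is well below 0.99, the sponsor will have to state a larger detectable effect for the 35 clinics. No new data or clinics are needed for the change itself.
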